**Exploratory**			
	To evaluate the association between engagement with PEAR-008 compared to reSET-O and treatment outcomes (abstinence and retention)	Daily and weekly use patterns; saliva (or urine drug screen for AREF^a^ participants only) and self-report; time to dropout	
	To evaluate skills acquisition at week 4 and week 8 of PEAR-008 compared to reSET-O	Cognitive Behavioral Therapy Skills Questionnaire	
	To evaluate medication adherence of PEAR-008 compared to reSET-O	Saliva drug screen (or urine drug screen, for AREF participants only)	

^a^AREF: Addiction Research and Education Foundation.

### Assessments

#### Demographics

Demographic information will be collected at the baseline session. Variables to be collected will include age at time of consent, sex assigned at birth, race and predominant self-reported ethnicity, level of education, marital status, employment status, occupation, and legal status.

#### Medical and Medication History

Medical history and current medical conditions, with current or prior treatment received, such as mental health disorders, hepatitis C virus, human immunodeficiency virus, and chronic pain syndromes, will be collected at the baseline session. Participant-reported history of substance use will be collected for the following substance categories: opioids, cocaine, stimulants (other than cocaine), alcohol, marijuana, benzodiazepines, other. Data to be collected regarding each substance include age at onset of use, number of years used regularly, amount used, type used (eg, pill vs powder), route of administration, history of overdose, and longest period of abstinence. Participant-reported history of substance use treatment will be collected, including present and prior treatment, type of treatment facility, number of treatment episodes, and current recovery activities. Nicotine use history will also be collected, including type, route, quantity, duration of use, and prior use. Medication history will include the name, dose, frequency, start and stop dates of the medication, and the indication for use. Prior or current medication for substance use disorder and opioid use disorder will also be recorded.

### Clinical Assessments

#### Abstinence From Opioids and Buprenorphine Adherence

Participant self-report of substance use and medication adherence will be collected within the reSET-O and PEAR-008 apps. In PEAR-008, participants are prompted to report use or abstinence each time they open the app as part of the check-in feature. In reSET-O, participants are prompted to report substance use or abstinence every 72 hours and can choose to self-initiate responses anytime.

Timeline followback will be completed at each virtual study session to assess patient-reported substance use since the time of the last assessment. The timeline followback is a validated calendar-based assessment used to obtain self-reports of amount and frequency of substance use retrospectively, using memory aids to enhance recall (eg, patterns of use, key dates).

Participants will self-administer a 12-panel saliva drug test during video sessions with study staff, who can assist in proper administration in addition to providing high-fidelity confirmatory testing. The 12-panel tests detect the presence of the following drugs: amphetamines, cocaine, cannabis, opioids, methamphetamine, barbiturates, benzodiazepines, buprenorphine, oxycodone, methadone, fentanyl, and alcohol. Saliva drug testing will be performed at the baseline session, once weekly during weeks 1-8 of the treatment phase and at the week 12 follow-up session. Participants will receive drug screening equipment regularly by mail.

When available, results of urine drug screening collected as part of routine care at participating treatment centers will also be used for participants recruited by AREF. All urine drug screen data are collected for clinical purposes and not as a study procedure. Urine drug screen results will be exported from the electronic medical record for inclusion in the study database. These data will be used to evaluate buprenorphine adherence and drug use. Results from additional urine drug screen confirmatory analyses for buprenorphine and norbuprenorphine may be available for some participants. When available, these data will be used to evaluate buprenorphine adherence.

#### Psychiatric Symptoms

Individuals with substance use disorders often experience psychiatric comorbidities, such as depression and anxiety. To evaluate the change in severity of co-occurring depression and anxiety symptoms, Patient Health Questionnaire–8 and Generalized Anxiety Disorder Questionnaire assessments will be delivered at baseline, week 4, week 8, and week 12.

The Patient Health Questionnaire–8 is an 8-item multipurpose instrument for screening and monitoring changes in depression [30]. The Generalized Anxiety Disorder Questionnaire–7 is a 7-item questionnaire for screening and monitoring changes in symptoms related to generalized anxiety disorder [31].

#### Recovery Status, Resilience, and Cognitive Behavioral Therapy Skills

The Substance Abuse and Mental Health Services Administration developed a working definition of recovery that includes 4 major dimensions: Health, Home, Purpose, and Community [32]. This definition highlights the importance of including measures of recovery across these dimensions in addition to substance use outcomes such as abstinence.

The Brief Assessment of Recovery Capital–10 is a 10-item assessment that will be used to measure participants’ level of recovery capital [33]. Recovery capital consists of a variety of resources and strengths that patients can use to support their recovery. The 4 major dimensions of recovery are thought to be strengthened as an individual builds recovery capital and may indicate an individual’s likelihood of remaining in remission [34].

The Connor-Davidson Resilience Scale–10 is a 10-item self-rating scale developed to assess resilience [35]. The measure is an abbreviated version of the 25-item version and was established on the basis of a factor analysis in a community sample. The questionnaire asks individuals to indicate how much they agree with a series of statements on a 5-point Likert scale. Resilience is a multidimensional trait characterized by an individual’s capacity to maintain normal functioning and resist the development of psychiatric symptoms and disorders in response to stress and adversity. The Connor-Davidson Resilience Scale will be used to evaluate the malleability and stability of trait resilience over courses of treatment with reSET-O and PEAR-008.

The Cognitive Behavioral Therapy Skills Questionnaire is a 16-item assessment that measures the use and acquisition of cognitive behavioral therapy skills during treatment [36] and is a validated measure of behavioral activation and cognitive restructuring. Development of skills that support behavior change is a key goal of cognitive behavioral therapy. This scale will be used to assess the development of cognitive behavioral therapy skills and whether there is a difference in skill development between individuals treated with reSET-O versus those treated with PEAR-008.

These scales will be administered at baseline, week 4, week 8, and week 12.

#### COVID-19 Impact

Two exploratory assessments will be used to evaluate the impact of the COVID pandemic on participants. The CAIR Pandemic Impact Questionnaire [37] is a 5-item assessment that measures how the COVID-19 pandemic is impacting participants, using a 5-point Likert scale to evaluate whether the respondent has experienced any growth changes related to COVID-19 in the past 2 weeks. A modified version of the Coronavirus Perinatal Experiences–Impact Survey asks participants how they are coping with stress related to COVID-19 from a list. The respondent is provided with a list of coping strategies and asked to select all strategies they have employed. Both assessments were selected from the PhenX Toolkit [38] and will be administered at baseline, week 4, week 8, and week 12.

#### Participant Motivation and Satisfaction

Participant motivation and satisfaction will be evaluated via surveys and qualitative interviews. Surveys will be administered at baseline, week 4, week 8, and week 12, with a range of questions designed to evaluate participant motivation (baseline only) and satisfaction with their assigned intervention (eg, ease of use, relevance, satisfaction).

A subset of participants (approximately 10 per treatment arm) will be asked to participate in a 1-on-1 qualitative interview to evaluate their respective experiences with each therapeutic, particularly ease of use and acceptability. Interviews will last approximately 60 minutes, be conducted by study staff, and will be performed remotely via video or phone. Interview transcripts will be coded and analyzed using grounded theory methodology to identify key themes. An inductive, open coding approach will be used to assign emerging categories. Emerging categories will be grouped to arrive at high-level themes during axial coding, and their properties and dimensions will be identified and described in a codebook.

### Data Management, Study Oversight, and Monitoring

Oversight of data management, including data collection, storage, export, security, tracking, data analysis, and quality assurance will be the responsibility of the study monitor designated by the study sponsor. Trial data will be managed with an electronic data capture system (Captivate, ClinCapture). Sites have access to this software as does the sponsor data monitor. Data collected by PEAR-008 and reSET-O are stored in the cloud. A data and safety monitoring board will provide additional oversight regarding the safety of study participants.

### Adverse Events and Safety Monitoring

The investigator or designee and research site staff will be responsible for the detection, documentation, classification, reporting, and follow-up of events that meet the definition of an adverse event or serious adverse event. Spontaneously reported or observed adverse events will be recorded throughout the study from the time of consent until the end of the last study visit. Adverse events will be elicited using a nonleading question at designated time points. Regardless of seriousness, intensity, or presumed relationship to reSET-O or PEAR-008, all adverse events will be recorded. The site investigator will monitor the occurrence of adverse events during the study.

Adverse events and serious adverse events will be collected and reported using the methods and definitions of the Office for Human Research Protections and National Institutes of Health (NIH) requirements for human participant protection. The investigator or designee is responsible for making an assessment as to the seriousness, intensity, causality, and outcome of an adverse event. The investigator will determine causality as related, possible, unlikely, or unrelated to reSET-O or PEAR-008.

### Confidentiality

Procedures to assure confidentiality will be strictly observed. All participant personal information will be kept confidential and will not be released without written permission, except as required by law. All study information will be kept separately from identifying information on consent forms and locator forms.

Data collected by the reSET-O and PEAR-008 system are securely transferred using industry standard encryption to a cloud-based infrastructure that serves and communicates with the patient facing mobile app; the backend services contain all data and analytics for reSET-O, PEAR-008, and clients (participants and clinicians). All data stored by the device are hosted and stored with a cloud-computing service (Amazon Web Services), which follows a variety of internationally recognized security standards, such as National Institute of Standards and Technology SP800-53 [39] and Health Insurance Portability and Accountability Act [40]. All patient information is automatically encrypted when it is entered into the system, which allows for secure data transfer (from patient device to clinician device) and storage.

In accordance with the 21st Century Cures Act [41], all ongoing or new research funded by NIH as of December 13, 2016 that collects or uses identifiable, sensitive information is automatically issued a Certificate of Confidentiality, which protects participants against disclosure of any sensitive information or illicit behavior (eg, drug use).

### Statistical Analysis

All statistical methods will be consistent with the International Conference on Harmonization E9 Guidance [42]. Data will be summarized by treatment group. For baseline, safety, and efficacy outputs a total population will combine both groups. Where appropriate, the data will be summarized by session in addition to treatment group. Baseline, demographic, and efficacy output data will be summarized by intended treatment. Safety output will be summarized by the treatment received.

Every effort will be made to obtain required data at each scheduled evaluation. Missing data will not be imputed. Sensitivity analyses incorporating various imputation assumptions may be performed if missing data exceed 5% of the total possible observations.

Descriptive statistics will be used to describe the population of study participants at the beginning of the study (mean, standard deviation, minimum, 25th percentile, median, 75th percentile, and maximum for continuous data; frequencies and percentages for categorical data). Differences in continuous variables will be summarized with Hedges *g* effect size; differences in categorical variables will be summarized with odds ratios.

### Endpoints

#### Primary Endpoint Analysis

Engagement with PEAR-008 and reSET-O will be defined as the number of active sessions per week. A session is defined as a set of in-app events with the same session ID. An active session is any session that contains some active participation in the app such as navigating to a different screen, engaging with a learning module, or responding to a notification. This endpoint was selected to allow a 1:1 comparison of content delivery method (eg, brief chapters vs longer lessons). The number of active sessions per week will be evaluated with a repeated measures mixed model of the form: *Number of Sessions in a Week = Week + Treatment + Week × Treatment + Subject Error + Random Error*. To evaluate the impact of treatment, this repeated measures mixed model will be compared to another of the form: *Number of Sessions in a Week = Week + Subject Error + Random Error* with a likelihood ratio test. The likelihood ratio test will be evaluated using model fit to maximize the log-likelihood.

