**Methods:**

Due to the COVID-19 pandemic, this study was redesigned using a decentralized model because it was not possible to conduct medication initiation and study visits in person, as initially intended. A decentralized, randomized controlled trial design will be utilized to compare patient engagement with PEAR-008 and that with reSET-O using both subjective and objective assessments. The study population will consist of approximately 130 individuals with opioid use disorder (based on Diagnostic and Statistical Manual of Mental Disorders 5 criteria) who have recently started buprenorphine treatment for opioid use disorder. Participants will be virtually recruited and randomly assigned to receive either PEAR-008 or reSET-O. All study sessions will be virtual, and the duration of the study is 12 weeks. The primary outcome measure of engagement is operationalized as the number of active sessions per week with either PEAR-008 or reSET-O. (An active session is any session that contains some active participation in the app, such as navigating to a different screen, engaging with a learning module, or responding to a notification.) Subjective dimensions of engagement will be assessed with participant surveys. The hypothesis is that PEAR-008 will have significantly greater participant engagement than reSET-O.

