### Study Population and Sample Size

The trial will include 130 adults aged 18 to 60 years with opioid use disorder who are already receiving buprenorphine treatment, with no criteria regarding gender identity, race, or ethnicity.

Inclusion criteria are having the ability to provide informed consent, age 18 to 60 years, having adequate English proficiency, being within the first 120 days of starting buprenorphine, receiving buprenorphine pharmacotherapy under the care of a licensed health care provider and being willing to provide the name of the provider or practice, being capable of using common software apps on a smartphone, and having access to an internet-enabled smartphone that meets minimal operating system requirements for the duration of the study. Exclusion criteria are having a history of reSET-O use, having participated in user-testing of PEAR-008 or any investigational drug trials within 30 days of trial enrollment, or currently receiving methadone or naltrexone pharmacotherapy.

The sample size and power were based on the primary engagement outcome, determined by frequency of interaction with the intervention, percentage of module completion, and approval ratings. A sample size of 130, α=.05, and power=0.80 will allow for detection of a moderate effect size (*d*=0.50).

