### Randomization and Blinding

Following informed consent, the baseline assessment and confirmation of eligibility, participants will be randomly assigned to 1 of 2 treatment groups: reSET-O or PEAR-008. Randomization lists will be prepared by the study sponsor (Pear Therapeutics) prior to the start of the study. Randomization will be 1:1 and stratified by site and gender with a block size of 10. An electronic list of IDs, access codes, and credentials will be securely provided to the sites. There will be no blinding; this is an open-label study.

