### Study Procedures

#### Overview

All study visits will be conducted remotely. Each prospective participant will complete a short screening assessment, and if basic eligibility is confirmed, complete informed consent procedures and sign an electronic informed consent form prior to completing the baseline assessment. After baseline assessments, participants will be randomly assigned to either reSET-O or PEAR-008 groups. Study staff will assist each participant with installation of their assigned digital therapeutic on their mobile device. Staff will provide training on the app’s use. Study participants will be enrolled for 12 weeks, with weekly virtual sessions during weeks 1-8 and a final visit at week 12, to evaluate the impact of reSET-O and PEAR-008 on participant engagement and treatment outcomes. Participants will also complete slightly longer assessments at weeks 4 and 8.

Weekly study assessments completed during the first 8 weeks of treatment include saliva drug screening (participants will receive drug screening equipment on a regular basis by mail; urine drug screen results may be retrieved from the electronic medical record for AREF participants), timeline followback [29], and adverse event reporting. Additional self-report assessments will be delivered at week 4 and week 8.

Participants will attend a virtual end of treatment study session at 12 weeks to complete the following: saliva drug screening, timeline followback, and adverse event reporting assessment. Additional measures will be assessed at the 12-week follow-up visit (Table 1).

**Table 1 table1:** Study objectives and endpoints.

Objective			Endpoint

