Treatment motivation and satisfaction will be evaluated based on individual participants’ rating of interest in using (baseline only), ease of use, satisfaction, perceived helpfulness, and likelihood of recommending reSET-O or PEAR-008. Descriptive statistics (mean, median, standard deviation) will be performed on Likert scale and multiple choice items that assess user satisfaction and attitudes about the patient mobile app. Analyses will be conducted on data collected at each assessment point throughout the study, ratings over the course of the study, and for overall user satisfaction as measured at the end of the study.

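### The written-out primary model has no baseline predictor, although interest in using the app is rated at baseline; adjusting for it could gain precision if interest predicts use, which the article does not show

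*Protocol article*

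**What the plan says.** The Primary Endpoint Analysis states: "The number of active sessions per week will be evaluated with a repeated measures mixed model of the form", and writes the full model out term by term: "Number of Sessions in a Week = Week + Treatment + Week × Treatment + Subject Error + Random Error". The reduced model for the likelihood ratio test keeps week and the two error terms and drops both treatment terms. Neither model holds a baseline variable.

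Under Participant Motivation and Satisfaction, surveys are given at baseline and weeks 4, 8 and 12, with motivation asked at baseline only. The Secondary Endpoint Analysis names the item, a "rating of interest in using (baseline only"), and plans descriptive statistics for the survey items.

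On timing, the Study Procedures overview says: "After baseline assessments, participants will be randomly assigned to either reSET-O or PEAR-008 groups". Randomization and Blinding gives the same order. It balances the arms on two factors only: "Randomization will be 1:1 and stratified by site and gender with a block size of 10".

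On size, the article says: "A sample size of 130, α=.05, and power=0.80 will allow for detection of a moderate effect size", with d=0.50.

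**The concern.** A participant cannot have a baseline value of the primary outcome. PEAR-008 is investigational, and prior reSET-O use is an exclusion. The usual gain from adjusting for the baseline outcome is therefore unavailable. Of the items the article says are recorded at baseline, the interest rating is closest in content to later use.

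If that rating predicts weekly active sessions, leaving it out keeps between-person variation in the arm comparison that could have been removed. Nothing in the design or analysis would then deal with a chance imbalance in motivation. The sample size leaves little margin above 80% power, so a few points would be worth having.

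The choice is open to review because the article states both models explicitly.

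**Working it through.** **Inputs from the article.** N=130 at 1:1, so 65 per arm; alpha 0.05; power 0.80; d=0.50 (Study Population and Sample Size; Randomization and Blinding). Model terms and test are from the Primary Endpoint Analysis.

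**Assumptions.**
- The test is two-sided. The article does not say, and the hypothesis is directional: "The hypothesis is that PEAR-008 will have significantly greater participant engagement than reSET-O".
- d is in SD units of a participant's mean weekly sessions.
- r, the correlation between baseline interest and mean weekly sessions, is not given; 0.1 to 0.5 is shown.
- Data are complete.

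**1. Reproduce the stated size.** For a two-sided two-sample t test, the noncentrality is d × √(n/2) = 0.5 × √32.5 = 2.850 on 128 df, and power is 0.808. The smallest n reaching 0.80 is 64 per arm (0.801), or 128 in total, against 130 planned. A one-sided test would need only about 50 per arm, so two-sided is the reading that fits. The normal approximation gives 0.813 at 65 per arm.

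**2. Adjust in a 1-df comparison.** A baseline covariate with correlation r multiplies the residual SD by √(1−r²), so the noncentrality becomes 2.850/√(1−r²). At r=0.3 this is 2.850/0.954 = 2.988. The one degree of freedom lost is ignored.

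**3. Adjust in the test specified.** The likelihood ratio test drops treatment and week × treatment together. That is 2 df if week is linear, or 1+11 = 12 df if week is categorical over 12 weeks; the article does not state the coding. With the whole effect a constant shift, the chi-square noncentrality is d² × n/2 = 0.25 × 32.5 = 8.125, divided by (1−r²) after adjustment.

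| r (assumed) | t test, 1 df | Joint test, 2 df | Joint test, 12 df |
|---|---|---|---|
| 0 (unadjusted) | 0.808 | 0.725 | 0.408 |
| 0.1 | 0.812 | 0.729 | 0.412 |
| 0.2 | 0.823 | 0.743 | 0.426 |
| 0.3 | 0.843 | 0.767 | 0.450 |
| 0.4 | 0.870 | 0.802 | 0.488 |
| 0.5 | 0.904 | 0.847 | 0.546 |

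At r=0.1 the gain is about 0.4 points in every column. At r=0.3 it is 3.5, 4.2 and 4.2 points.

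**4. Where the gain falls.** The rating does not change over time. As a main effect it cancels from within-person differences between weeks. With complete weekly data it therefore sharpens the average treatment contrast and gives the week × treatment part essentially nothing. The joint-test columns are favourable to adjustment because they place the whole effect in the constant shift.

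**5. Chance imbalance.** The standardised difference between arms in any baseline rating has SD √(2/65) = 0.175, so about one trial in 20 exceeds 1.96 × 0.175 = 0.34. At r=0.3 that moves the outcome difference by 0.3 × 0.34 = 0.10 SD, one-fifth of 0.50. The unadjusted test already allows for this in its error rate; adjustment would remove it from the estimate in hand.

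**The case against.** The strongest reply is that this is a preference and no error has been shown. A randomised comparison without covariates is valid, the stated power is met for the calculation that reproduces it, and choosing an optional prognostic covariate is often left to an analysis plan. The first two parts stand: there is no bias, contradiction or wrong figure here. The third carries less weight because the article fixes both models term by term.

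A reader might infer that power is demonstrably being wasted. The article does not support that. It gives no correlation and no variance components. All participants volunteered for an app trial, so ratings may cluster high and predict little.

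A reader might also take 82–90% as the adjusted power of the primary analysis. Those figures belong to a 1-df t test. The test specified starts lower, and part of it does not benefit.

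Finally, adjustment might be called free of any risk to validity. That depends on timing. The trial is open-label, the item is worded as interest in reSET-O or PEAR-008, and the article's statements on the order of events do not name this survey. If it were answered once the arm was known, adjusting would condition on a response to allocation. This objection stands until the timing is confirmed.

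**Conclusion.** The point holds as a minor, optional improvement in efficiency. A candidate baseline covariate is already collected, by the stated order before randomisation, and the primary model does not use it. The benefit ranges from nothing at zero correlation, through about 4 points of power at r=0.3, to about 10 points (1-df comparison), 12 points (2 df) or 14 points (12 df) at r=0.5. Every r is assumed, and the joint-test figures also assume a constant effect over the weeks. No single figure can be defended from the article. Omitting the covariate does not bias the comparison and does not make the sample size statement wrong.

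**What to change.** - Confirm and state that the interest rating is completed before the participant learns the allocation. If that cannot be confirmed, leave it out of the model.
- If it is confirmed, add the rating as a prespecified fixed covariate to both the full and the reduced primary model, so that the degrees of freedom of the likelihood ratio test do not change.
- State how a missing rating is handled. Filling it with the overall mean keeps every participant in the model, but the Statistical Analysis section rules out imputation in general terms. Say that this baseline covariate is an exception and that the rule otherwise concerns outcomes.
- Report the unadjusted model as a sensitivity analysis.

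The change needs wording in the protocol's primary analysis and in the analysis plan, and no new data collection. It costs one degree of freedom, with little or no return if the rating is weakly prognostic or varies little. It should be made before any comparison by arm is seen, since a covariate added later in an open-label trial would look chosen from the data.
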